### Data registration

Data will be entered into the web-based electronic Case Report Form (eCRF) (RedCap, Vanderbilt University, Nashville, TN, USA) by trial or clinical personnel under the supervision of the trial site investigators at each participating center. The following data reported to influence the outcome of kidney transplantation will be registered at the different stages of the procedure:➢ In donors with a beating heart:○ Demographic data (age, sex, Body Mass Index (BMI), ethnic group, cause of death)○ Significant medical history (chronic kidney disease, hypertension, diabetes, alcohol abuse)○ Detailed SOFA score in the last 24 h before organ harvesting○ Significant biochemical abnormalities: hypernatremia > 160 mmol L^−1^, coagulation abnormalities (disseminated intravascular coagulation)○ Renal function, assessed by blood urea nitrogen levels, creatininemia and 24-h creatinine clearance in the last 24 h prior to the harvesting○ Immunological and viral status: Epstein-Barr virus (EBV) serology, number of HLA incompatibility➢ During kidney harvesting, preservation and transplantation○ Preservation data: type of preservation solution, use of a perfusion machine, cold ischemia time○ Intraoperative data: hemodynamic stability (systolic blood pressure < 80 mmHg, need for vasopressors), warm ischemia time, technical problems (duration of anastomose, surgical difficulties, hemorrhage)➢ In transplanted patients○ Demographic data (age, sex, BMI, blood group, ethnic characteristic)○ Significant medical history: hypertension, cardiac failure, diabetes, cause of the kidney disease, previous transplantation(s), duration of dialysis before transplantation, duration on the transplantation waiting list○ Viral (C hepatitis) and immunological (anti-donor antibodies) status○ Dialysis during the first week after transplantation○ Creatininemia and estimated creatinine clearance (MDRD) on days 1, 3 and 7 after transplantation○ 24-h urine output on days 1, 3 and 7 after transplantation○ Recipient and graft survival at 1 year

### Data handling and retention

Data will be handled according to French law. All original records (including consent forms, reports of suspected unexpected serious adverse events, and relevant correspondences) will be archived at the trial sites for 15 years. The trial database will be anonymized and maintained for 15 years.

### Enrollment and timeline

2015 to 2017: protocol, approvals from the ethics committee and trial tool development (eCRF, randomization system).

2017 to 2019: inclusion of patients from 16 French University Hospitals.

2019: cleaning and closure of the database.

Early 2020: data analyses, writing of the manuscript and submission for publication.

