### Outcomes

➢ Primary outcome: rate of DGF defined by the need for at least one dialysis session within the first 7 days after kidney transplantation➢ Secondary outcomes:○ Rate of SGF defined by a urine output of less than 1000 mL on day 1 after transplantation, or a decreased of less than 30 and 70% in creatinine plasma concentration, respectively, on days 3 and 7 after transplantation○ Combined rate of DFG + SGF○ Mild DGF defined by a serum creatinine reduction ratio from post-transplant day 1 to day 2 less than or equal to 30% plus 24-h urine creatinine excretion on day 2 greater than 1000 mg○ Severe DGF defined by a serum reatinine reduction ratio from post-transplant day 1 to day 2 less than or equal to 30% plus 24-h urine creatinine excretion on day 2 less than or equal to 1000 mg○ Duration of in-hospital length of stay (post-transplantation hospitalization)○ Daily urine output on days 1, 3 and 7○ Creatininemia and estimated creatinine clearance by the Modification of Diet in Renal Disease (MDRD) formula [17] on days 1, 3 and 7○ Rate of primary graft dysfunctions on day 1 defined by the absence of immediate renal function (anuria)○ Time between transplantation and normalization of graft function in patients presenting a DGF○ Function of kidney transplants at 1 year: kidney graft dysfunction defined by a clearance creatinine less than 30 mL min^−1^ estimated by the MDRD formula or total dysfunction defined by a persistent hemodialysis○ In-hospital and 1-year mortality rate of transplanted patients

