## Trial status

The study has been recruiting since 19 December 2017.

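### The timeline closes the database in 2019 while inclusion runs into 2019, so recipients transplanted in 2019 reach the 1-year secondary outcomes only after closure

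*Protocol article*

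**What the plan says.** The calendar is in the Protocol article, Enrollment and timeline. Three of its lines matter here:

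- inclusion: "2017 to 2019: inclusion of patients from 16 French University Hospitals"
- closure: "2019: cleaning and closure of the database"
- analysis: "Early 2020: data analyses, writing of the manuscript and submission for publication"

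The Trial status section fixes the actual start: "The study has been recruiting since 19 December 2017".

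The Outcomes section lists two late secondary outcomes: "In-hospital and 1-year mortality rate of transplanted patients" and "Function of kidney transplants at 1 year: kidney graft dysfunction defined by a clearance creatinine less than 30 mL min" (per minute, by the MDRD formula), with persistent hemodialysis counted as total dysfunction. The Data registration section includes "Recipient and graft survival at 1 year" among the items to be entered in the eCRF. The abstract and the Background also name 1-year renal function and mortality among the secondary objectives.

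The primary outcome is short-term: "rate of DGF defined by the need for at least one dialysis session within the first 7 days after kidney transplantation".

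The article gives one closure. It mentions no follow-up period between the end of inclusion and that closure, and no second lock for the 1-year data.

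**The concern.** A database that holds 1-year outcomes for every recipient cannot close before the last recipient has passed 1 year. Here inclusion and closure fall in the same calendar year, and analysis follows a few months later. If the timeline is followed as written, every recipient transplanted in 2019 lacks a 1-year value at closure, however complete the site follow-up is.

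At stake are 1-year graft function and 1-year mortality, the only outcomes in the list tied to a late fixed time point. The article's rationale rests partly on long-term prognosis, so these are the outcomes that speak to it. The Sample size section compares categorical secondary outcomes by chi-squared or Fisher's exact test. Those tests need a known status at 1 year and cannot use a partial follow-up time. Because the gap comes from the calendar alone, it can be prevented entirely.

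**Working it through.** **The plan's own figure.** For 30% against 20%, two-sided alpha 0.05 and 80% power, with pooled variance under the null hypothesis:

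n per group = [1.96·√(2·0.25·0.75) + 0.8416·√(0.30·0.70 + 0.20·0.80)]² / 0.10² = (1.2002 + 0.5119)² / 0.01 ≈ 293.2, rounded up to 294.

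This matches the article's 294 per group (588). Then 294 × 1.1 = 323.4, rounded up to 324, and 2 × 324 = 648, the stated total. The calculation uses only the 7-day outcome, so the closure date does not enter it. Below, 648 serves only as the denominator.

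**The contradiction, without assumptions.** The earliest transplantation in 2019 is on 1 January 2019, and its 1-year date is 1 January 2020. The latest closure in 2019 is 31 December 2019. So no recipient transplanted in 2019 reaches 1 year before closure.

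**Its size, with assumptions.** Inputs from the article: start on 19 December 2017, closure in 2019, 648 recipients. Assumptions: uniform accrual, closure on 31 December 2019 (the most favorable date), and an end of inclusion varied across 2019, because the article gives only the year.

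With that closure, only recipients transplanted by 31 December 2018 have reached 1 year. From 19 December 2017 to 31 December 2018 is 377 days. With T the number of days from the start to the end of inclusion:

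share without a 1-year value = (T − 377) / T

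| End of inclusion | T (days) | Share | Of 648 |
|---|---|---|---|
| 1 January 2019 | 378 | 1/378 = 0.3% | 2 |
| 31 March 2019 | 467 | 90/467 = 19% | 125 |
| 30 June 2019 | 558 | 181/558 = 32% | 210 |
| 30 September 2019 | 650 | 273/650 = 42% | 272 |
| 31 December 2019 | 742 | 365/742 = 49% | 319 |

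**Earlier closure.** With closure on 30 June 2019, only the first 193 days of accrual (to 30 June 2018) have reached 1 year. The share is then (378 − 193)/378 = 49% (317) if inclusion ends on 1 January 2019, (467 − 193)/467 = 59% (380) at end March, and (558 − 193)/558 = 65% (424) at end June.

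**Cost in precision.** If variance scales as 1/n and other losses are ignored, the standard error of a 1-year comparison grows by √(648 / number with a value). For closure on 31 December 2019 this is √(648/523) = 1.11 for an end in March, √(648/438) = 1.22 in June, √(648/376) = 1.31 in September and √(648/329) = 1.40 in December.

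**Closure date that would work.** The last 1-year date is 31 March, 30 June, 30 September or 31 December 2020 for an end of inclusion on the same day of 2019. Cleaning comes after that, so analysis in early 2020 does not fit any of these either.

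**The case against.** The strongest reply is that the section is a coarse calendar in whole years, not a rule for the lock. The Outcomes and Data registration sections call for the 1-year data independently, so the likely practical correction is that closure slips, and a staged lock could well be described in a full protocol that is not shown. That stands as a reason for moderation. It does not remove the contradiction, because the article does more than leave a detail out: it states one closure, dates it, and the date conflicts with its own outcomes.

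A second reply is that inclusion may end at the very start of 2019, which brings the share close to zero. The wording allows this, but it is not the natural reading. It would need all 648 recipients within about 12 months of the start, with closure and any cleaning after the last visits squeezed into the last days of 2019. It belongs in the range as the lower limit.

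Uniform accrual is also only an assumption. Sixteen centers may not open together, and slower early accrual would raise the share.

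Some stronger inferences do not hold:

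- *Bias between arms.* A reader might infer that the treatment comparison is biased. Allocation is 1:1 in permuted blocks, stratified by center and number of kidneys, so missingness set by calendar date should be roughly balanced between arms.
- *Counting short follow-up as success.* A reader might infer that recipients short of 1 year would be treated as alive with a functioning graft. Nothing in the article says so.
- *Breach of the 10% loss allowance.* The Sample size section mentions both primary and secondary endpoints there, but the allowance inflates a calculation made for DGF. It sets no tolerance for administrative censoring at 1 year.

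**Conclusion.** The inconsistency is real and limited in scope. With inclusion running into 2019 and a single closure in 2019, the 1-year secondary outcomes fall after closure for every recipient transplanted in 2019. That conclusion needs only the article's own dates.

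The size depends on when in 2019 inclusion ends. Under uniform accrual and the latest possible closure it runs from about 0% to 49% of recipients, and it is higher if closure is earlier. The consequence is loss of precision and completeness for 1-year graft function and mortality.

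A reader might infer that the trial's main result is at risk, or that the 1-year values can never be obtained. Neither follows. The primary outcome is complete by day 7 and the sample size rests on it alone. The 1-year values would still arise; they would simply fall after the stated closure. This should be fixed, as a matter confined to secondary outcomes.

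**What to change.** Either of two changes resolves it:

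1. **One later closure.** Set final closure no earlier than 12 months plus a visit window after the last recipient's transplantation, and move the early-2020 analysis and submission accordingly.
2. **Two locks.** State a first lock for the day-7 and in-hospital outcomes and a later one for 1-year graft function and mortality, and state that no 1-year analysis is run before the second lock.

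Both need a timeline amendment. The first delays all reporting. The second adds a lock and a second round of cleaning but need not delay the primary result. Neither changes the sample size or the primary analysis.

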## Discussion

Transplantation represents the best option to improve the prognosis and the quality of life of end-stage renal disease patients. Delayed graft function may complicate this procedure and thus worsens significantly the long-term prognosis. Numerous interventions failed to decrease the rate of this complication [8, 18]. This trial investigates the potential benefits of a pharmacological preconditioning procured by cyclosporine A. The dose of this molecule selected in our study (2.5 mg kg^−1^) is lower than that used in immunosuppressive protocols. Actually, the inhibition of PTP opening is achieved with low doses and does not involve an immunosuppressive effect. Moreover, previous clinical trials used this dosage without adverse effects, particularly on renal function [19]. The time of administration of cyclosporine is a critical question. Numerous studies have reported the deleterious effects of ischemia-reperfusion with the majority of lesions occurring during reperfusion. Thus, the best protective effects were obtained with different interventions before ischemia and/or reperfusion [9, 10]. In the transplantation model, this objective will be reached with the administration of cyclosporine A in the brain-dead donor before harvesting of the kidneys. In this case, cyclosporine A will be present at the site of effect before ischemia and reperfusion. Last, we selected the renal transplantation model because the kidney is the most frequently grafted organ. Moreover, the occurrence of DGF represents a significant complication impeding the short- and the long-term prognosis. An intervention decreasing this complication will improve the outcome of renal transplantation, which has major public health implications.

## Trial status

The study has been recruiting since 19 December 2017.

## Abbreviations

BMI: Body mass index
DGF: Delayed graft function
PTP: Permeability transition pore
SGF: Slow graft function
